### Medical history

For all participants document the below information:

- Any history suggestive of CF
  - - Number of chest infections, wet cough, constipation, greasy stools, faltering growth
- Feeding history (breast/bottle/mixed and estimated percentage of each)
- Achievement of age-appropriate developmental milestones
  - Specifically, assessing for achievement of milestones prior to limit ages for areas of gross motor, vision and fine motor, hearing, speech and language, and social behaviour (see details in appendix 2 based on Lissauer, T. and Clayden, G., 2015. *Illustrated textbook of paediatrics*. 4th ed. Edinburgh: Elsevier)(27)
- Medication history
- Has there been continued/new exposure to CFTR modulators:
  - - In-utero (No, Yes (timing and months of exposure))
    - Breast feeding while mother on CFTRm (No, Yes (timing and months of exposure)

### Physical examination

At all visits carry out the below examinations using local procedures:

- Weight in kilograms (and plot centile)
- Head circumference in centimetres (and plot centile) if below the age of two.
- Blood pressure in millimetres of mercury (and plot centile)
- Document any abnormalities detected in a general examination including the cardiovascular, respiratory, abdominal, and neurological systems.

### Liver function blood tests

A heel/toe prick device will be used to obtain around 1ml of capillary blood into an SST bottle and sent to the local laboratory for analysis for liver function tests (ALT, ALP, AST, Gamma-GT, total bilirubin, conjugated bilirubin, unconjugated bilirubin, and albumin). In circumstances where parents prefer venepuncture over a heel prick this will be an option. Tests will be analysed as per local lab procedures.

Three monthly liver function tests are our local standard of practice for infants with continued exposure to CFTRm in the first year. The blood test temporally closest to the study visit will be recorded. If any abnormalities are found, there may be a requirement for more regular testing. This will also be recorded.

For infants not exposed to CFTRm this test is for research purposes only, and as with all other tests optional.

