## Primary Objectives

1. **Sub-study ‘Mama’**
   1. To record the obstetric and neonatal outcomes of females with CF.
   2. To record CF-related health outcomes among females with CF including pulmonary (e.g. ppFEV_1_) and nutritional status (e.g. BMI) during pregnancy and early parenthood (up to 24 months).
   3. To record the subjective experiences of family planning, pregnancy and early parenthood in females with CF.
   4. To describe the impact of diabetes (pre-existing and gestational) on obstetric, neonatal and CF related outcomes.
   5. To record sweat chloride results during pregnancy and/or lactation among females with CF in relation to CFTR modulator therapy.
2. **Sub-studies ‘Mini’ and ‘Midi’**
   1. To collate clinically obtained serum liver enzymes levels and to record the frequency of congenital abnormalities (including ophthalmic cataract screening), in children born to a parent with CF (females or males with CF).
   2. To document cases of ‘missed’ CF-diagnoses due to false negative immunoreactive trypsinogen (IRT) results in children of females with CF in relation to transplacental and/or lactational exposure to CFTR modulators.
   3. To record lung function using lung clearance index (LCI) for young children (aged three-to-six years) born to a parent with CF.

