## ‘Mini’ and ‘Midi’ sub-study assessments

### Summary flow chart of study assessments (Table 2 & 3)

‘Mini’ Sub-Study (Table 2)

A phone or video call will take place before the first in-person visit to review inclusion/exclusion criteria and will be repeated in person at the first visit.

There are no strict time-windows in which each visit must be completed, but preferably they should be as close as possible to the designated visit. If a participant is enrolled at an older age than 8 weeks (for example any age up to 12 months), all the procedures from Visit 1 should still take place at the first visit, with the schedule then proceeding as below.

| Study Procedure | Visit 1  4-8 weeks age | Visit 2  6 months of age | Visit 3  12 months of age | Visit 4  24 months of age |
| --- | --- | --- | --- | --- |
| **For all children enrolled** | | | | |
| Informed consent | X |  |  |  |
| Inclusion/exclusion criteria | X |  |  |  |
| Demographics | X |  |  |  |
| Baseline assessments^1^ | X |  |  |  |
| Medical History^2^ | X | X | X | X |
| Physical examination^3^ | X | X | X | X |
| Liver function blood tests^4^ | X | X | X^5^ | X^5^ |
| Sweat test^6^ | X | X^7^ |  |  |
| Faecal elastase^8^ | X | X^7^ |  |  |
| Cranial ultrasound^9^ | X |  |  |  |
| **Only for children exposed to CFTRm** | | | | |
| Document ophthalmological review^10^ | X |  | X^5^ | X^5^ |
| CFTRm assay^11^ | X | X | X^5^ | X^5^ |
| **Key**:  X: Planned completion date  Highlighted in grey: tests that are additional to standards of practice. Note that all tests for children not exposed to CFTRm are additional to standards of practice.  1. See section 9.4.2  2. See section 9.4.4.  3. See section 9.4.5.  4. See section 9.4.6  5. Only if breastfed and exposed to CFTR modulator in last 6 months  6. See section 9.4.8  7. If exposed to CFTRm via breast feeding at the 4 – 8 weeks visit to repeat at 6 months. If still exposed at 6 months repeat at 12 months and so on, as exposure to CFTRm via lactation could affect results  8. See section 9.4.9.  9. See section 9.4.10  10. See section 9.4.3  11. See section 9.4.7 | | | | |

‘Midi’ Sub-study (Table 3)

As for ‘Mini’, a phone or video call will take place before the first in-person visit to review inclusion/exclusion criteria and will be repeated in person at the first visit.

All tests for all participants in the ‘Midi’ study are additional to standards of practice.

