### Cranial ultrasound (‘Mini’ sub-study only)

A consultant paediatric radiologist will carry out a focussed cranial ultrasound scan at the first infant visit at 4 – 8 weeks of age. If not carried out in visit one, this can also be carried out at visit 2 (6 months of age). There will also be the opportunity for repeat scans dependent on initial findings, radiologist availability and parental preferences.

This purpose of this scan is to assess for changes indicative of raised intracranial pressure (which has been described as a possible side effect of childhood use of ETI). This will include measurements of the fluid spaces within the baby’s brain and of blood flow within the arterial system of the brain. The scan will take around five minutes.

There is no associated radiation risk with ultrasound. The scan is not uncomfortable for the baby with an ultrasound probe lightly placed on the anterior fontanelle. If needs be, the scan can be performed whilst the baby is cradled. If the baby is uncomfortable for other reasons and cannot easily be settled the scan will not proceed and can be rearranged. This scan also raises the possibility of incidental findings of unclear significance. These findings will be discussed as appropriate with a paediatrician to create a management plan.

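### Liver results in continuously exposed infants are recorded only near study visits or after an abnormality, so the primary liver count is incomplete, partly outcome-dependent and uneven against non-exposed infants

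*Protocol*

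**What the plan says.** Protocol 9.4.6 states the clinical background: "Three monthly liver function tests are our local standard of practice for infants with continued exposure to CFTRm in the first year". The recording rule follows: "The blood test temporally closest to the study visit will be recorded". One addition is made: "If any abnormalities are found, there may be a requirement for more regular testing. This will also be recorded".

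Table 2 (9.4.1) puts the 'Mini' visits at 4-8 weeks, 6, 12 and 24 months. Liver tests are scheduled for every child at Visits 1 and 2. At Visits 3 and 4 they carry a footnote: "Only if breastfed and exposed to CFTR modulator in last 6 months". A non-exposed infant therefore has two scheduled tests. The same section says there are no strict visit windows.

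The first 'Mini'/'Midi' primary objective (5.2) begins "To collate clinically obtained serum liver enzymes levels". The matching primary endpoint (15.2.1) is the number of participants with ALT, AST, GGT or bilirubin above the upper limit of normal, obtained prospectively in 'Mini'. Section 15.4.2 plans chi-square or Fisher's exact tests between exposed and non-exposed groups for categorical variables.

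**The concern.** A three-monthly series yields more tests in the first year than there are visits, so some routine results have no visit to attach to. Under 9.4.6 such a result leads to study data only if it is abnormal and prompts further testing. A normal result does not enter, nor does a mild rise that prompts nothing. The text also leaves open whether the result that set off the extra testing is entered, or only the tests that came after it.

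The endpoint is a per-infant count of ever being above a limit. Such a count depends on how many tests are kept for each infant and on why they were kept. If keeping a test depends partly on its result, and exposed infants have more tests than non-exposed infants, the count in exposed infants is hard to interpret and its comparison with non-exposed infants is not like with like.

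The rises of interest may be short. The background (4.2.2) describes an exposed infant whose ALT peaked at 65 U/L and settled by day 158.

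**Working it through.** The protocol gives no power or sample-size figure for this endpoint (15.3.1), so there is nothing to reproduce. Three checks follow.

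**1. Tests without a visit, first year.** The start of the three-monthly cycle is not stated, so two readings are shown.
- Cycle counted from birth, plus Visit 1: about weeks 6, 13, 26, 39 and 52. Visits match weeks 6, 26 and 52. Unmatched: 2 of 5.
- Cycle counted from Visit 1: about weeks 6, 19, 32 and 45. Closest to the 6-month visit is 19 or 32; closest to 12 months is 45. Unmatched: 1 of 4.

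**2. Chance that a transient rise overlaps a kept test.** Assumptions, none from the documents: onset uniform over the first year, fixed duration D, and no credit for the recorded follow-up of abnormalities. A test at time t catches onsets between t − D and t, so capture is the length of the union of these intervals within the year, divided by the year.

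For D = 8 weeks:
- Visit-matched (6, 26, 52): (6 + 8 + 8)/52 = 22/52 = 42%.
- All tests, cycle from birth: (13 + 8 + 8 + 8)/52 = 37/52 = 71%.
- Cycle from Visit 1: kept tests 22/52 = 42% (whether week 19 or 32 is kept); all four (6 + 8 + 8 + 8)/52 = 30/52 = 58%.
- In months, D = 2, tests at 1.5, 3, 6, 9 and 12: kept (1.5 + 2 + 2)/12 = 46%; all (3 + 2 + 2 + 2)/12 = 75%.

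| Duration | From birth: kept | From birth: all | From Visit 1: kept | From Visit 1: all |
| --- | --- | --- | --- | --- |
| 4 weeks | 23% | 38% | 23% | 31% |
| 8 weeks | 42% | 71% | 42% | 58% |
| 12 weeks | 58% | 94% | 58% | 81% |
| 16 weeks | 73% | 100% | 67% | 87% |

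**3. Uneven opportunity between groups.** With k independent tests, each abnormal with probability p and no true effect of exposure, P(at least one abnormal) = 1 − (1 − p)^k. The values of p are assumed.

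| p | k = 2 (non-exposed) | k = 3 (exposed, visit-matched, year 1) | k = 5 (exposed, every abnormal result entering) |
| --- | --- | --- | --- |
| 0.05 | 9.8% | 14.3% | 22.6% |
| 0.10 | 19.0% | 27.1% | 41.0% |

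The ratio of k = 5 to k = 2 is 22.6/9.8 = 2.3 and 41.0/19.0 = 2.2. That is the upper end for the five-test reading, since it assumes every off-visit abnormality reaches the study. Even the visit-matched count is uneven once Visit 3 is included.

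**Other routes into the data.** Medical history (9.4.4) lists no liver results. Section 12.2 strictly requires CRF entry only for adverse events possibly related to study procedures. Section 12.4 sends modulator-related liver dysfunction to the Yellow Card scheme. Section 12.6 documents extra investigations for medical issues that arise, which again starts from a problem. None covers a normal or mildly raised off-visit result.

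**The case against.** The best defence is that 9.4.6 is a sensible visit-matching rule. It spares infants a further heel prick, gives aligned time points, and does not say that other results are excluded. The results stay in the hospital notes, from which the CRF draws (13.2), and a statistical analysis plan is still to be written (13.3). Clinically important abnormalities would in practice be retested, recorded and documented under 12.4 and 12.6. The objective speaks of collating clinical levels, not all of them.

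Much of this stands, and it limits what can be claimed:
- A reader might infer that the 3- and 9-month results are thrown away. Those ages appear nowhere in the protocol. The local procedure is a separate document (6.1), visits have no strict windows, and the results remain retrievable from the notes.
- A reader might infer that all exposed infants are affected. The three-monthly practice applies only to those with continued exposure, a subset of unstated size within the 25-35 infants expected (15.3.2).
- A reader might infer that the liver frequency has no proper denominator. The endpoint counts infants, so infants are its denominator; missing normal results do not alter that count.
- A reader might take the background ALT case as a demonstrated miss. Day 158 precedes the 6-month visit (about day 183), but no onset date is given, so the rise may already have been present at 4-8 weeks.

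What does not stand is leaving the matter to the analysis plan. This is a data-capture rule, and a plan cannot analyse results that the CRF did not collect.

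**Conclusion.** The point holds in a limited form. In infants with continued exposure, the stated rule leaves about 1 of 4 to 2 of 5 first-year liver tests outside the study record unless an abnormality prompts more testing, and the status of the triggering result is unclear. Ascertainment of the primary liver count is incomplete, partly dependent on the outcome, and uneven against non-exposed infants.

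The direction of any net bias is not settled. Unrecorded mild rises lower the exposed count, while extra tests that enter because they are abnormal raise it relative to the non-exposed group. The 42-46% capture of an 8-week rise is a lower bound on what the protocol would achieve, because it ignores the follow-up pathway. Like the 58-75% for all tests, it rests on assumed onset, duration and schedule. The figures show scale and are not a forecast.

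**What to change.** Amend 9.4.6 so that every clinical liver result in the first two years is entered, normal or abnormal, with date, value, reason (routine or follow-up of an abnormality) and exposure status. This settles whether a triggering result is recorded. Flag the visit-matched result as a separate variable.

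Base any exposed versus non-exposed comparison on visit-matched tests at the time points common to both groups, Visits 1 and 2. Report all results in exposed infants descriptively, with the number of tests per infant, and do not set that count against the non-exposed count.

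The cost is a little extra transcription from records already held, in a small cohort. Record review is already planned for this endpoint in 'Midi' (15.2.1). No sampling is added and clinical testing does not change.

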### Blood test for CFTRm assay and serum save

During the same procedure as the liver function blood tests, around 200 microliters of blood will be collected for qualitative and quantitative analysis of CFTRm and their major metabolites using LC-HRMS or LC-MS/MS and storage. If there is remaining sample, it will be stored and frozen for potential future analysis of other tests if emerging research suggests this is necessary.

### Sweat chloride testing

A small electrical current is applied to the forearm, following which a collecting device is used to collect up to 0.5ml of sweat over a 20 - 30-minute period. This is done on both forearms in parallel. The sample will be sent and processed by our local laboratory.

### Faecal elastase

A stool sample will be collected by parents in a universal container and sent to the local laboratory for quantification of faecal elastase levels.

### Cranial ultrasound (‘Mini’ sub-study only)

A consultant paediatric radiologist will carry out a focussed cranial ultrasound scan at the first infant visit at 4 – 8 weeks of age. If not carried out in visit one, this can also be carried out at visit 2 (6 months of age). There will also be the opportunity for repeat scans dependent on initial findings, radiologist availability and parental preferences.

This purpose of this scan is to assess for changes indicative of raised intracranial pressure (which has been described as a possible side effect of childhood use of ETI). This will include measurements of the fluid spaces within the baby’s brain and of blood flow within the arterial system of the brain. The scan will take around five minutes.

There is no associated radiation risk with ultrasound. The scan is not uncomfortable for the baby with an ultrasound probe lightly placed on the anterior fontanelle. If needs be, the scan can be performed whilst the baby is cradled. If the baby is uncomfortable for other reasons and cannot easily be settled the scan will not proceed and can be rearranged. This scan also raises the possibility of incidental findings of unclear significance. These findings will be discussed as appropriate with a paediatrician to create a management plan.

### Lung clearance index (LCI) (‘Midi’ sub-study only)

A qualified RBH physiologist will use an Exhalyzer D to perform a multiple breath washout (MBW) test and provide a lung clearance index (LCI) report(28,29). LCI, the primary derivative from MBW, is a measure of the efficiency of gas mixing within the lungs and an indicator of ventilation inhomogeneity. It is a sensitive measure in detecting peripheral airway changes in children. The test requires relaxed tidal breathing while the child breathes in 100% oxygen for a few breaths. It is repeated to obtain three reliable trials, in which the mean result is taken as the LCI result. Overall, this should take around 20 – 30 minutes.

### Oxygen (O_2_)-enhanced Lung MRI (‘Midi’ sub-study only)

At the visit when the child is between 5 – 6 years of age an O_2_-enhanced MRI of the child’s lungs will be undertaken to assess for any structural or functional changes. The study team is experienced in performing these scans on children of this age. Before the MRI is performed, the study team will confirm that the child does not have any contraindications to MRI using the local MRI safety checklist. If the child is unable to tolerate the MRI for any reason, the procedure will not go ahead. Again, sedation is not an option on this study. Headphones with music and other calming measures will be provided to increase comfort in the scanning machine and a parent is encouraged to remain in the scanner room to keep the child calm. Information from the RBH clinical specialist ‘play team’ will be provided in advance to allow some pre-scan preparation.

The MRI scan will take 20 – 40 minutes and will involve a short period of breathing 100% oxygen via a facemask. If any abnormalities are detected on the scan, they will be discussed with the paediatricians on the study team and any appropriate further investigation or follow-up arranged. Families will be consented about the risk of false positive or incidental findings. There is no associated radiation risk with MRI scans.

# Definition of the End of Study

Completion of the last participant’s last visit.

# Discontinuation/withdrawal of participants

Participants are able to withdraw at any time point. They will be able to request their data are removed from the study. Data that has been anonymised and merged will not be able to be removed, including samples which have been stored for block analysis.

# Safety Reporting

## Definition

**Adverse Event (AE)** — any untoward medical occurrence in a patient or clinical study subject who is participating in a study.

**Serious Adverse Event (SAE)** – is defined as an untoward occurrence that:

- Results in death; or
- Is life-threatening (places the subject, in the view of the Investigator, at immediate risk of death)
- Requires hospitalization or prolongation of existing hospitalization (hospitalisation is defined as an inpatient admission, regardless of length of stay; even if it is a precautionary measure for observation; excluding hospitalisation for an elective procedure, for a pre-existing condition)
- Results in persistent or significant disability or incapacity (substantial disruption of one’s ability to conduct normal life functions)
- Consists of a congenital anomaly or birth defect (in offspring of subjects or their parents taking the study drug regardless of time of diagnosis)
- Is otherwise considered medically significant by the investigator.

Important medical events that may not be immediately life-threatening or result in death or hospitalisation but may jeopardise the subject or may require intervention to prevent one of the outcomes listed in the definition of serious will also be considered serious.

## Recording Adverse Events (AEs)

This study is an observational study with no treatment provided. The investigator will discuss with the participant whether there have been any occurrence of AEs. Only AEs deemed to be (possibly) related to the study procedures need to be strictly recorded in the medical records and CRF. These should be recorded in full including the duration (start and end dates), severity (Table 4), outcome, treatment provided, and relation to study procedures (Table 5), as well as if it meets the definition of an SAE.

Non-study procedure related AE’s can be recorded in the medical records if felt to be clinically significant. Any AEs felt to be related to CFTRm should be reported via the national Yellow Card Scheme.

**Table 4. AE Severity grading**

| Severity | Description |
| --- | --- |
| Mild | Asymptomatic or mild symptoms; clinical or diagnostic observations only; intervention not indicated |
| Moderate | Minimal, local or non-invasive intervention indicated; limiting daily activities. |
| Severe | Medically significant but not immediately life-threatening; hospitalization or prolongation of hospitalization indicated. Unable to perform daily activities. |
| Life-Threatening | Life-threatening consequences: urgent intervention indicated. |
| Death | Death related to AE. |

**Table 5. AE relationship to study procedure**

| Relationship | Description |
| --- | --- |
| Unrelated | There is no evidence of any causal relationship |
| Unlikely | There is little evidence to suggest there is a causal relationship (e.g. the event did not occur within a reasonable time after study procedure). There is another reasonable explanation for the event (e.g. the participant’s clinical condition, other concomitant treatment). |
| Possibly | There is some evidence to suggest a causal relationship (e.g. because the event occurs within a reasonable time after study procedure). However, the influence of other factors may have contributed to the event (e.g. the participant’s clinical condition, other concomitant treatments). |
| Probably | There is evidence to suggest a causal relationship and the influence of other factors is unlikely. |
| Almost certainly | There is clear evidence to suggest a causal relationship and other possible contributing factors can be ruled out. |

